## Abstract

**Background:**

For decades, planar bone scintigraphy has been the standard practice for detection of bone metastases in prostate cancer and has been endorsed by recent oncology/urology guidelines. It is a sensitive method with modest specificity. ^18^F-fluoride positron emission tomography/computed tomography has shown improved sensitivity and specificity over bone scintigraphy, but because of methodological issues such as retrospective design and verification bias, the existing level of evidence with ^18^F-fluoride positron emission tomography/computed tomography is limited. The primary objective is to compare the diagnostic properties of ^18^F-fluoride positron emission tomography/computed tomography versus bone scintigraphy on an individual patient basis.

**Methods/Design:**

One hundred forty consecutive, high-risk prostate cancer patients will be recruited from several hospitals in Denmark. Sample size was calculated using Hayen’s method for diagnostic comparative studies. This study will be conducted in accordance with recommendations of standards for reporting diagnostic accuracy studies. Eligibility criteria comprise the following: 1) biopsy-proven prostate cancer, 2) PSA ≥50 ng/ml (equals a prevalence of bone metastasis of ≈ 50 % in the study population on bone scintigraphy), 3) patients must be eligible for androgen deprivation therapy, 4) no current or prior cancer (within the past 5 years), 5) ability to comply with imaging procedures, and 6) patients must not receive any investigational drugs. Planar bone scintigraphy and ^18^F-fluoride positron emission tomography/computed tomography will be performed within a window of 14 days at baseline. All scans will be repeated after 26 weeks of androgen deprivation therapy, and response of individual lesions will be used for diagnostic classification of the lesions on baseline imaging among responding patients. A response is defined as PSA normalisation or ≥80 % reduction compared with baseline levels, testosterone below castration levels, no skeletal related events, and no clinical signs of progression. Images are read by blinded nuclear medicine physicians. The protocol is currently recruiting.

**Discussion:**

To the best of our knowledge, this is one of the largest prospective studies comparing ^18^F-fluoride positron emission tomography/computed tomography and bone scintigraphy. It is conducted in full accordance with recommendations for diagnostic accuracy trials. It is intended to provide valid documentation for the use of ^18^F-fluoride positron emission tomography/computed tomography for examination of bone metastasis in the staging of prostate cancer.

## Background

Prostate cancer is one of the most frequent cancers in men [1]. It often metastasises to the bone, and this is associated with significant morbidity and mortality [2, 3]. According to current urology and oncology guidelines, planar bone scintigraphy (BS) remains the standard practice for detection of bone metastases in prostate cancer [4–6]. BS has a high sensitivity for detection of bone metastases in the staging of prostate cancer while its specificity is moderate. Activity on BS may also represent benign conditions such as degenerative bone disorders, traumas and inflammatory conditions [7]; these conditions frequently occur in older men diagnosed with prostate cancer [8].

Technical development within nuclear medicine bone imaging has emerged since the introduction of BS, including single photon emission computed tomography/computed tomography (SPECT/CT), acquisition of BS, and positron emission tomography/computed tomography (PET/CT) with ^18^F-fluoride and ^18^F- or ^11^C-choline [9, 10]. The principle of ^18^F-fluoride is somewhat similar to BS since it reflects regenerative bone processes, not the bone metastasis itself. However, compared with the BS tracer, ^18^F-fluoride has a higher bone uptake, a faster blood clearance and an improved target-to-background ratio [11]. Furthermore, PET is associated with higher spatial resolution than gamma-camera-based BS and likely may improve diagnostic accuracy [11–13].

Retrospective studies, often with a limited number of patients, have indicated that ^18^F-fluoride PET/CT is superior to BS for detection of bone metastases in patients with newly diagnosed prostate cancer and patients with recurring prostate cancer. However, in the absence of histopathological verification, the definitions of presence or absence of bone metastases are essential for interpretation of diagnostic comparative studies. A recent systematic review identified this issue as a key methodological flaw in studies with bone-targeting PET ligands [10]. Thus, the advantage of ^18^F-fluoride PET versus BS for the diagnosis of bone metastases remains to be shown in well-designed studies.

The primary aim of this diagnostic test accuracy study is to compare ^18^F-fluoride PET/CT versus guideline-recommended BS in diagnosing bone metastases in newly diagnosed prostate cancer. The study protocol is in full compliance with recommendations for diagnostic test accuracy studies [14, 15]. Particular attention is aimed at applying an optimised reference standard, i.e., confirming the presence or absence of bone metastases.

## Methods/Design

### Study objectives

The primary objective of this study is to assess the diagnostic accuracy of ^18^F-fluoride PET/CT for detection of bone metastases compared with BS in newly diagnosed, high risk, untreated prostate cancer patients on an individual patient basis.

Secondary objectives are: 1) to assess the diagnostic properties of SPECT/CT in comparison with BS and ^18^F-fluoride PET/CT, 2) to evaluate the diagnostic properties of all imaging modalities on the basis of individual lesions, 3) to investigate the inter- and intra-observer variation of SPECT/CT and ^18^F-fluoride PET/CT, and 4) to investigate the predictive role of bone tumour load as measured by ^18^F-fluoride PET/CT as a predictor of time to loss of hormone sensitivity.

### Study design

This study is designed as a multicentre, single-group, prospective diagnostic test accuracy (DTA) study. It will be conducted according to methodological criteria and recommendations as outlined by Standards for Reporting of Diagnostic Accuracy studies (STARD) [14] and the Grading of Recommendation, Assessments, Development and Evaluation (GRADE) [15].

Within a time window of 14 days, and no later than 7 days after initiation of androgen deprivation (ADT), consenting patients will be examined by BS, SPECT/CT and ^18^F-fluoride PET/CT. These scans are baseline examinations (Table 1). To assist in determination of equivocal lesions on the baseline scan, the response to treatment will be examined after 6 months of ADT. Studies indicate regression of bone metastasis within 6 months following ADT in prostate cancer [16–21], notable decrease of baseline PSA within 6 weeks [16] and testosterone levels below castration levels (≤50 ng/mL) within 4 weeks. The time period of 6 months should be sufficient to demonstrate notable treatment effects without any influence of the short-lasting, treatment-induced osteoblastic response called the flare phenomenon [22, 23].

**Table 1 Tab1:** Overview of study procedures

	Baseline		Follow-up	
Visit number:	1	1a	2	2a
Day:	0	1	180	181
Androgen deprivation theapy	Ongoing			
Planar bone scintigraphy	X		X	
SPECT/CT	X		X	
^18^F-fluoride PET/CT		X		X
PSA	X		X	
P-testosterone	X		X	

Following 6 months of ADT, patients with a satisfactory response will have all three scans repeated (Table 1). A satisfactory ADT response is defined as: 1) normalisation of PSA or at least 80 % reduction of baseline PSA levels, 2) plasma-testosterone below castration levels, 3) no skeletal-related events since baseline, and 4) no clinical, biochemical, or other indication of disease progression. The imaging response to satisfactory ADT will guide the readers to classify metastasis and benign lesions on the baseline scans (Fig. 1). ADT affects both the primary tumour and bone metastatic cancer cells, and bone metastases will therefore regress or become indistinguishable on imaging following satisfactory ADT [29, 30] (Fig. 2). The patients will be followed clinically until the cancer has progressed to castration-resistant prostate cancer according to criteria from the European Association of Urology [26].

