### Study population

A total of 140 consecutive patients will be recruited. Eligibility criteria comprise: 1) biopsy-proven prostate cancer, 2) PSA ≥50 ng/ml, 3) patients must be eligible for androgen deprivation therapy, 4) no current or prior cancer (within the past 5 years), 5) ability to comply with imaging procedures, and 6) no investigational drugs. Based on existing data, the prevalence of bone metastases in this population is expected to be approximately 50 % on BS [8]. A bone metastasis-enriched population was selected to optimise sample size while still taking into consideration obtaining a reference test. Inclusion of patients scheduled for prostatectomy or radiation therapy would interfere with the definitions of the reference standard and presence or absence of bone metastasis (see Rationale for design).

Subjects will be recruited consecutively from, at present, four urological departments in Denmark.

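### Patients without a satisfactory ADT response have no stated reference diagnosis, so verification is incomplete and tied to treatment outcome

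*Protocol article*

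**What the plan says.** Study design restricts the six-month imaging: "Following 6 months of ADT, patients with a satisfactory response will have all three scans repeated". A satisfactory response has four conditions. They include "normalisation of PSA or at least 80 % reduction of baseline PSA levels" and "no skeletal-related events since baseline"; the other two are castrate testosterone and no sign of progression.

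The abstract (Methods/Design) says "All scans will be repeated after 26 weeks of androgen deprivation therapy", and the same sentence goes on: "response of individual lesions will be used for diagnostic classification of the lesions on baseline imaging among responding patients". Table 1 puts PSA and testosterone at the day-180 visit, together with the repeat BS and SPECT/CT. It shows no study sample between baseline and that visit.

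Final diagnosis calls a lesion read as malignant at baseline a true positive if it responded on any follow-up image, and a false positive if it responded on none. False negatives and true negatives follow from how the lesion is classified on the other modalities. A patient with at least one malignant lesion on any modality is classified as malignant.

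Study design also states: "The patients will be followed clinically until the cancer has progressed to castration-resistant prostate cancer".

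**The concern.** Read together, these sections give a reference diagnosis to responders and none to anyone else. The joint all-modality reading for equivocal cases (Follow up images) also uses follow-up scans, so it is no way out for a patient who is not rescanned.

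The loss is unlikely to be random. Skeletal-related events and progression plausibly go with metastatic burden. The protocol itself treats a link between visible bone disease and failure of ADT as plausible: its fourth secondary objective studies bone tumour load on PET/CT as a predictor of time to loss of hormone sensitivity. The verified set would then be selected, after the index tests, on something related to what those tests measure. Absolute sensitivity, predictive values and prevalence would describe that set rather than the 140 consecutive patients.

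**Working it through.** **Inputs from the document (Sample size considerations).** 140 recruited, 114 needed, prevalence 50% on BS, sensitivity 0.87 for both BS and PET/CT. The 114 cannot be reproduced, because the false positive fractions and the paired agreement are not given. It implies 114 × 0.5 = 57 patients without metastases; 140 recruited implies 70. The allowance for all losses is 26/140 = 18.6%, described as being for dropouts.

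**Assumptions (not in the document).** Specificity 0.75; 10 or 20 patients without a satisfactory response, all metastatic and all detected at baseline.

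**Case A: they are left unverified.** Start from 70 metastatic (TP = 70 × 0.87 = 60.9, FN = 9.1) and 70 non-metastatic (FP = 17.5, TN = 52.5), then subtract the lost patients from TP.

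| Lost | Sensitivity | Specificity | PPV | NPV | Prevalence |
|---|---|---|---|---|---|
| 0 | 60.9/70 = 0.870 | 52.5/70 = 0.750 | 60.9/78.4 = 0.777 | 52.5/61.6 = 0.852 | 70/140 = 0.500 |
| 10 | 50.9/60 = 0.848 | 0.750 | 50.9/68.4 = 0.744 | 0.852 | 60/130 = 0.462 |
| 20 | 40.9/50 = 0.818 | 0.750 | 40.9/58.4 = 0.700 | 0.852 | 50/120 = 0.417 |

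Specificity and NPV do not move. If both modalities detect the lost patients, both sensitivities fall together and their difference stays at zero. These are concordant pairs and add nothing to the McNemar counts.

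**Case B: response unrelated to detection.** Assume specificity 0.70 and a satisfactory response in 70% of metastatic patients, detected or not, and in 95% of the others. Then TP = 60.9 × 0.7 = 42.63, FN = 9.1 × 0.7 = 6.37, FP = 21 × 0.95 = 19.95 and TN = 49 × 0.95 = 46.55.

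- Sensitivity: 42.63/49 = 0.870, unchanged.
- PPV: 42.63/62.58 = 0.681, against 60.9/81.9 = 0.744 with everyone verified.
- Prevalence: 49/115.5 = 0.424.
- Specificity: 46.55/66.5 = 0.70, unchanged, with 66.5 non-metastatic patients left against the 57 implied.

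So PPV and prevalence shift whenever metastatic patients respond less often. Sensitivity shifts only if non-response is linked to visibility on the scan.

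**Case C: they are rescanned and the Final diagnosis rule is applied.** Return to specificity 0.75 and suppose that no lesion regresses in these 10 or 20 patients. Each becomes a non-metastatic patient with a positive scan. Apparent specificity is 52.5/80 = 0.66 or 52.5/90 = 0.58. If both modalities are positive in them, the discordant counts stay as they were, but the difference in false positive fractions shrinks by a factor of 70/80 = 0.875 or 70/90 = 0.778.

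**The case against.** Nowhere does the article say that non-responders leave the analysis; that is an inference. Study design describes follow-up as an aid for equivocal lesions and as guidance to the readers. Follow up images has them weigh baseline characteristics along with change. The SAP, not shown, may deal with patients who lack a reference result. This stands as a limit on wording. It does not remove the gap: the true- and false-positive definitions need follow-up images, and the topics the article hands to the SAP (multiple lesions, inconsistent responses between modalities, secondary endpoints) do not include non-responders. Who is rescanned is also a data-collection rule, and a scan that was never done cannot be recovered by analysis.

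A reader might infer that the trial recreates the flaw for which it faults earlier work, "because of methodological issues such as retrospective design and verification bias". That goes too far. Verification here depends on treatment response, not on the index test result, so incomplete verification is the accurate term.

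A reader might also infer that the powered comparison is undermined or that the 26-patient allowance is overrun. The trial is powered on false positive fractions. In Cases A and B specificity is unchanged and the number without metastases stays above 57. Specificity would move under Case C, or if response among non-metastatic patients depended on the scan result.

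The illustration in Case A is an extreme one, with every lost patient metastatic and detected. Its shift of 2 to 5 points in sensitivity also lies within the sampling error of 0.87 on 70 patients (1.96 × √(0.87 × 0.13/70) = 0.08). That is fair as to size, although a selection effect is systematic and the confidence interval does not cover it.

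The conflict between the abstract and Study design may be loose wording: all scans can mean all modalities, and PSA may be known from routine care before day 180. One clarifying sentence settles either.

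**Conclusion.** The point holds as one of incomplete verification tied to treatment outcome. As written, patients without a satisfactory ADT response have no stated route to a reference diagnosis, and the existing lesion rule would mislabel true metastases if it were applied to them.

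If non-responders are more often metastatic, prevalence and PPV among verified patients fall. Absolute sensitivity falls too if non-response goes with scan-visible burden. The figures in Case A rest on assumed counts and an assumed specificity; the document gives no non-response rate. The documents do not support a claim that the specificity comparison or the paired PET/CT versus BS result is lost when such patients are simply dropped.

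Study population also says "Inclusion of patients scheduled for prostatectomy or radiation therapy would interfere with the definitions of the reference standard", although none of the six numbered criteria names such patients. That is a separate, minor wording matter and adds no weight here.

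**What to change.** 1. Reconcile the abstract, Study design and Table 1 on who is rescanned, and on how response is established when PSA and testosterone are drawn at the same visit as the repeat BS and SPECT/CT.
2. State in Final diagnosis that the rule equating no response with a false positive does not apply to patients without a satisfactory response.
3. Keep the responder-based analysis. Add a prespecified analysis of all enrolled patients with baseline scans, in which non-responders are classified from the available imaging and the clinical follow-up already planned. Give best- and worst-case bounds for those who remain unclassifiable.
4. Report the number of unverified patients and their baseline results on each modality.

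The cost is protocol and SAP wording, a small amount of extra reading and one further analysis. The price in validity is a softer reference standard for non-responders: it leans on the index tests, and later progression does not by itself prove bone metastases at baseline. That is why the all-enrolled analysis is proposed as an addition and not as a replacement. The trial is listed as recruiting, so the change can still be made before analysis.

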**Fig. 1 Fig1:**
[figure not shown]
Schematic drawing of the treatment response of planar bone scintigraphy and ^18^F-fluoride PET/CT. **a** Baseline imaging with planar bone scintigraphy (BS); BS shows two lesions in the pelvic region, one lesion in a vertebra, and lesions at both hip joint surfaces. **b**
^18^F-fluoride PET/CT demonstrate two additional lesions that were not detected by BS (marked with blue circle). **c** Post-ADT imaging with BS. **d** Post-ADT imaging with ^18^F-fluoride PET/CT. All lesions detected by BS, which are not located near joints, showed partial (*n* = 2) or complete (*n* = 1) regression and thus were defined as bone metastases. All the lesions detected by ^18^F-fluoride PET/CT, which are not located near joints, regressed (*n* = 5). Thus, ^18^F-fluoride PET/CT detected two lesions that were not detected by BS, these are defined as true positive on^18^F-fluoride PET/CT and consequently as false negative on BS. *ADT* androgen deprivation therapy. The illustration is copyright of Nuclear Medicine Aalborg

### Study population

A total of 140 consecutive patients will be recruited. Eligibility criteria comprise: 1) biopsy-proven prostate cancer, 2) PSA ≥50 ng/ml, 3) patients must be eligible for androgen deprivation therapy, 4) no current or prior cancer (within the past 5 years), 5) ability to comply with imaging procedures, and 6) no investigational drugs. Based on existing data, the prevalence of bone metastases in this population is expected to be approximately 50 % on BS [8]. A bone metastasis-enriched population was selected to optimise sample size while still taking into consideration obtaining a reference test. Inclusion of patients scheduled for prostatectomy or radiation therapy would interfere with the definitions of the reference standard and presence or absence of bone metastasis (see Rationale for design).

Subjects will be recruited consecutively from, at present, four urological departments in Denmark.

### Ethical considerations

This DTA study will be conducted according to the principles of the Helsinki II Declaration. The patients receive oral and written information about the study and provide written informed consent prior to any study-related procedures. The study protocol is approved by the North Denmark Region Committee on Health Research Ethics (N-20130068) and the Danish Data Protection Agency.

### Imaging procedures

#### Planar bone scintigraphy and SPECT/CT

BS and SPECT/CT is conducted in accordance with current institutional recommendations which are in line with international guidelines [27]. Whole body BS is performed 2 h after injection of approximately 750 M Becquerel (MBq) 99^m^Tc-labelled diphosphonate. Three-bed SPECT/CT torso-scan (from vertex to mid-thigh) is performed immediately after BS. The CT component used with SPECT as well as with PET is a low-dose acquisition primarily used for attenuation correction and anatomical localisation.

### ^18^F-fluoride PET/CT

^18^F-fluoride PET/CT will be conducted in accordance with recent American and German guidelines [28, 29]. PET/CT will be performed approximately 30 min after intravenous administration of 200 MBq ^18^F-fluoride. A total of 7 to 9 bed positions are performed with an acquisition time of 2.5 min per bed position resulting in a scan from the skull to mid-thigh.

### Image analysis

Diagnostic accuracy is primarily analysed on a patient-basis. All images are evaluated by a reading committee of two readers who must be board certified in Nuclear Medicine and/or Radiology and experienced with the imaging modality. Readers will have access to PSA, T-stage, Gleason grade, and a standard questionnaire filled out by the patients. The amount of clinical information will be minimised to reduce reading bias but the amount of information will be sufficient to reflect clinical practice and thus, will present the generalisability of the findings. The questionnaire contains information about any artificial joint replacements, prior surgeries to joint or bone, prior skeleton or joint infections, known degenerative or inflammatory bone diseases, recent trauma to the skeleton, and location and duration of any bone pain [8].

All lesions, or a representative sample if a large number of lesions are present, are first classified independently by each reader for malignancy using a dichotomous scale as well as a numerical rating scale which includes an equivocal rating option [30]. The latter scale will be used primarily to determine observer agreement. Eventually, the readers will reach consensus for the dichotomous outcome. If consensus cannot be reached, a third reader will be included and a majority rule will apply. Lesion analysis is then summarised on an individual patient basis. The exact measurement scales and how to handle patients with multiple bone lesions will be stated in a reader manual and the statistical analytical plan (see Data Analysis). Readers may participate in the reading committee for more than one imaging modality.

### Image evaluation procedure

#### Baseline images

A standardised protocol for image analysis will be used. As a rule of thumb, the following applies: 1) lesions located in the pelvis or spine, which are not directly joint-related (e.g., sacroiliac joint, facet joints, or discs) are malignant, 2) isolated lesions outside the pelvic/hip area, with no simultaneous uptake in the axial skeleton, are benign; however, if concurrent metastases in the axial skeleton are present, malignancy is considered, 3) lesions in hands, feet, and at large joints (shoulders, elbows, hips joints, and knees) are benign.

Even though the use of low-dose CT is primarily for attenuation correction and anatomical localisation, any diagnostic information obtained from the CT scan will be used, e.g., the characteristics and extent of osteosclerotic and osteolytic lesions, lesion irregularity, etc.

